
### Covariates

Sociodemographic factors (age, sex, residency, marital status, education, income status, and employment), lifestyle behaviors (smoking and drinking), and health conditions (visual status, diagnosed with hypertension, diabetes, or any other cardiovascular diseases, and self-reported health) of the eligible participants are collected during the baseline survey.

### Statistical Analysis

The intent-to-treat principle will be used during the impact analysis. The differences between the control and intervention groups in terms of primary and secondary outcomes will be evaluated through ANOVA and linear mixed-effects modeling. Multiple methods such as weighting, matching, and imputation will be used to handle the problem of missing data and sample attrition. In addition, a nonparametric bias-corrected case resampling bootstrap method, structural equation modeling, or interaction analysis will be used to further explore the buffering effect of psychosocial factors. Heterogeneity analysis will be applied to investigate whether the intervention effects are robust across subgroup samples, such as participants with different levels of objective hearing loss.

The cost-effectiveness analysis will be based on the costs of the HAU or HHE interventions and their effects on improving health-related quality of life, as measured by EQ-5D-5L. EQ-5D-5L is designed to measure the generic quality of life in terms of mobility, self-care, usual activities, pain or discomfort, and anxiety or depression [49]. Previous literature has used this multidimensional construct of quality of life to evaluate the effect of hearing interventions [50-53].

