**Results:**

Participants were recruited for hearing tests in September 2022, during which baseline results were collected through in-person interviews. Follow-up interviews were conducted in September 2024. The primary analysis will use ANOVA, linear mixed-effects modeling, structural equation modeling, and cost-effectiveness analysis.

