### Sample Size Calculation and Recruitment

Sample size calculations are based on the expected effects of the hearing aid intervention on the primary outcome: an individual’s functioning in society measured by the World Health Organization Disability Assessment Schedule 2.0 (WHODAS 2.0), which was developed within the ICF conceptual framework [34]. We estimate that a sample size of 222 (111 participants in each group) provides 85% statistical power with a 5% significance level to detect a standardized effect size of 0.404 for the difference between the HAU group and the control group in the mean change from baseline in the functioning score at the 24-month follow-up [23]. Since there is little evidence evaluating the effects of HAU on social isolation using the Lubben Social Network Scale (LSNS), or the effectiveness of HHE on functioning and social isolation, we will assign the HHE group the same sample size as the HAU group and the control group. To account for a 20% drop-in (uptake of hearing aids in the control group) and dropout (discontinuation of HAU in the hearing intervention group) rate, a total of 435 individuals are included. This comprises 121 individuals in the HAU group, 158 in the HHE group, and 156 in the control group, respectively. Recruitment activities are conducted in communities and villages (n=8) from Guangzhou, Shanwei, Chaozhou, and other areas in Guangdong Province, China. The recruitment of participants commenced on September 1, 2022, and was completed on September 31, 2022. Oral informed consent is obtained through prescreening, and written informed consent is presented by the investigator to the participant before the hearing screening. Hearing screening and assessment will be undertaken by an audiologist following a standardized procedure (Table 1).

**Table 1 table1:** Schedule of enrollment, interventions, and assessments.

Time point				Study period																												
				Enrollment T_1_						Allocation T_0_					Postallocation T_1_							Postallocation T_2_						Close-out T_4_				
				–30 to –1 Day						Day 0					6 months							12 months						24 months				
				T^a^		T^b^		C^c^		T	T		C		T		T		C		T			T		C	T			T		C
Enrollment																																
Eligibility screen				✓		✓		✓																								
Informed consent				✓		✓		✓																								
Demographics				✓		✓		✓																								
Health history				✓		✓		✓																								
Visual status				✓		✓		✓																								

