### Randomization, Allocation, and Masking

After confirming eligibility and informed consent, participants are randomly stratified by HI severity and the field site to ensure a balanced distribution of participants. Randomization is performed by an independent statistician who is not involved in data collection, management, or analysis using a computer-generated random number sequence to assign participants to either the treatment or control group [35]. Allocated interventions will not be modified unless participants voluntarily withdraw for personal reasons. Due to the nature of the interventions, complete blinding of participants and facilitators is not feasible. However, we minimize the potential biases by blinding participants to the study hypothesis, using standardized protocols for training and tools for measurement, and masking field staff to allocation details.

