Third, the provision of free hearing aids may raise concerns regarding the social approval effect. Previous research on hearing aid interventions has typically involved the distribution of free devices [51,58,59]. In instances where there is a financial burden associated with acquiring commercial hearing aids, selection bias may arise, as economically disadvantaged older individuals may find it more challenging to participate in such interventions. The Chinese government has established a range of welfare policies aimed at supporting individuals with disabilities and the elderly, which include not only rehabilitation services, but also living subsidies for disabled individuals, long-term care insurance, and older adult care subsidies. Within this welfare framework, hearing aids do not represent a unique benefit. Therefore, we contend that the social approval effect remains within a manageable scope and is unlikely to compromise the reliability and validity of the RCT. Future research could also compare the intervention effects of paid hearing aids with those of free hearing aids.

Fourth, the interventions are conducted at different sites, which may result in geographical and selection biases. Nevertheless, the comparable socioeconomic and cultural contexts of these sites are expected to alleviate such biases. There was no pilot study due to time and budget constraints; however, given that the social and demographic characteristics of the feasibility study site closely resemble those of the formal trial sites, we believe this limitation does not pose a significant threat to the research design.

Fifth, our reliance on self-reported measures of social isolation and functioning may introduce measurement bias, which we will address through the use of validated tools, cross-validation, and multisource evaluations.

Lastly, although the sample size was determined using standard calculation methods, it remains relatively small, which affects its representativeness and external validity. Randomization in a small sample may not completely eliminate the preexisting differences either. Therefore, we will further use matching techniques or other econometric methods during the statistical analyses.

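### The group comparison names ANOVA and a mixed model with neither ruling, states no baseline or stratum term, and lists matching beside intention to treat; one baseline-adjusted primary analysis should be fixed for HHE versus control

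*Protocol article*

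**What the plan says.** On the between-group comparison, Protocol article, Statistical Analysis: "The differences between the control and intervention groups in terms of primary and secondary outcomes will be evaluated through ANOVA and linear mixed-effects modeling". The sentence before it reads: "The intent-to-treat principle will be used during the impact analysis". The sentence after it reads: "Multiple methods such as weighting, matching, and imputation will be used to handle the problem of missing data and sample attrition". The same section then gives structural equation modeling an exploratory role (the buffering effect of psychosocial factors) and describes cost-effectiveness separately, based on EQ-5D-5L. Severity of hearing loss appears there only as an example of a subgroup.

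The Results paragraph of the Abstract groups these differently: "The primary analysis will use ANOVA, linear mixed-effects modeling, structural equation modeling, and cost-effectiveness analysis".

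Three other places bear on the choice of model:
- Randomization, Allocation, and Masking: "participants are randomly stratified by HI severity and the field site to ensure a balanced distribution of participants".
- Sample Size Calculation and Recruitment: the effect is a difference "in the mean change from baseline in the functioning score at the 24-month follow-up".
- Limitations, on differences that randomization may leave: "Therefore, we will further use matching techniques or other econometric methods during the statistical analyses".

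Study Design and Setting places the primary outcome measurements at baseline and 24 months. Table 1 shows pure-tone audiometry at baseline in all three arms.

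**The concern.** Two methods stand side by side for the same comparison, and either could be reported as the main result. ANOVA itself can be run on 24-month scores or on change. The power calculation points to change, but the analysis text does not say. These versions respond differently to a baseline difference, so the choice can move the estimate.

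The baseline outcome and the severity stratum are in hand for every participant and should enter the primary comparison. A trial that stratifies its allocation normally carries the strata into the model.

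Matching is given two purposes: missing data in Statistical Analysis, and pre-existing differences in Limitations. It does not recover a missing outcome. Its common forms keep only matched participants, which would change the population estimated. The article does not reconcile this with intention to treat.

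Follow-up was collected in September 2024, and the current protocol version, of January 2025, says that effects are still unknown. The ruling analysis should be fixed while that remains so.

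**Working it through.** **1. The plan's own figure.** Inputs from Sample Size Calculation and Recruitment: standardized effect 0.404 on change from baseline, 85% power, 5% significance (taken as two-sided).

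n per arm = 2 × ((1.960 + 1.036) / 0.404)² = 110.02, rounded up to 111. This reproduces the stated 111 per group. One-sided testing would give 89, so the calculation is two-sided.

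**2. Is power short without adjustment?** For HAU versus control at the sizes enrolled (121 and 156), power for a change-score comparison is 0.915. With 397 of 435 followed up (91.3%, assumed equal across arms) it is 0.890. It is not short.

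**3. Variance by method.** With unit SD at both visits and correlation r:
- ANOVA on 24-month scores: 1
- ANOVA on change: 2(1 − r)
- ANCOVA on baseline: 1 − r²
- ANCOVA relative to change: (1 − r²) / (2(1 − r)) = (1 + r)/2

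The article gives no r, so it is assumed. The n column is 110.02 × (1 + r)/2, rounded up, with 0.404 in change-score SD units as the protocol defines it.

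| r (assumed) | ANCOVA / change | ANCOVA / 24-month ANOVA | n per arm, ANCOVA | Power at 111 per arm, ANCOVA |
|---|---|---|---|---|
| 0.5 | 0.75 | 0.75 | 83 | 0.935 |
| 0.6 | 0.80 | 0.64 | 89 | 0.920 |
| 0.7 | 0.85 | 0.51 | 94 | 0.904 |

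The change-score analysis has power 0.853 at 111 per arm. The gain equals 1/0.85 = 1.18 to 1/0.75 = 1.33 times the participants. Over the wider range r = 0.3 to 0.8, ANCOVA needs 72 to 100 per arm instead of 111. The factor (1 + r)/2 is below 1 for any r below 1, so only the size of the gain depends on r.

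**4. What a baseline difference does.** If the arms differ by D at baseline, ANOVA on 24-month scores is shifted by rD and ANOVA on change by −(1 − r)D. With D = 0.2 SD (assumed) and r = 0.4 to 0.8:
- 24-month scores: 0.2 × 0.4 = 0.08 to 0.2 × 0.8 = 0.16 SD
- change: 0.2 × 0.6 = 0.12 down to 0.2 × 0.2 = 0.04 SD, in the opposite direction

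ANCOVA removes the part that runs through the baseline score.

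**5. Observed imbalance, HHE versus control (Table 2).**
- Good self-rated health: 149/157 = 94.9% versus 76/156 = 48.7%. Standardized difference = 0.462 / √((0.949×0.051 + 0.487×0.513)/2) = 1.20.
- Age: (74.82 − 71.44) / √((9.29² + 6.51²)/2) = 3.38/8.02 = 0.42.

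Self-rated health is plausibly related to functioning as WHODAS 2.0 measures it. Table 2 gives no baseline WHODAS 2.0 or LSNS-6 values.

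**6. Origin of the arms (Study Design and Setting).** HHE and control come from one county and include any degree of impairment. HAU comes from persons with disabling impairment at four sites, drawn from a provincial register. Site, and largely severity, therefore goes with arm in HAU versus control. With no overlap in site, no covariate or weight can separate the two.

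**The case against.** The strongest reply is that a condensed article is silent on model terms because the full analysis plan holds them. That stands for the fixed effects and covariates of the mixed model: their absence alone is not an error. It does not cover what the article does state, which is ANOVA as a method for the comparison, two methods with no precedence, and matching as a missing-data remedy.

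A reader might also infer more than the text supports:
- **That the plan leaves the baseline outcome out.** The powered quantity is change from baseline, and a two-visit mixed model can hold the baseline value. The text states no baseline term; it does not exclude one.
- **That matching will drop randomized participants.** It is one example beside weighting and imputation, no discard rule is given, and full matching drops nobody.
- **That imbalance is left uncorrected.** The Limitations section plans matching or other econometric methods for it. The plan is loose, but it exists.
- **That there are four rival primary analyses.** Only the Abstract reads that way. The body separates the roles.
- **That ANOVA is shown to be biased here.** Without baseline WHODAS 2.0 or LSNS-6 by arm, no difference in the outcomes themselves is demonstrated. Step 4 is an illustration.

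It can also be said that adjusting for baseline score, severity and site would miss the largest gap in Table 2. That is right, and is why self-rated health belongs in the model. A gap that wide (chi-square 82.6 on 1 df) is hard to put down to chance, so its coding should be checked. Adjustment does not explain it.

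**Conclusion.** The point holds as a choice of method that should be improved and fixed. The article leaves two methods for the primary comparison without a ruling one, states neither a baseline nor a stratum term, and sets matching beside intention to treat without reconciling them. The Abstract's label for structural equation modeling and cost-effectiveness disagrees with the body.

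That ANCOVA is at least as precise as either ANOVA follows from the variance formulas, assuming equal SDs at the two visits. The size, an error variance 0.75 to 0.85 of the change-score analysis, rests on an assumed r of 0.5 to 0.7. It should not be read as showing that the trial is underpowered: 111 per arm reproduces, and the enrolled numbers give more than 85% for the powered contrast under the retention assumed above.

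Nor should the better model be read as a rescue of HAU versus control. There, site and source population are confounded with arm by the way the arms were drawn, and neither adjustment nor weighting removes that.

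**What to change.** For HHE versus control, name one primary analysis: ANCOVA of the 24-month score in all allocated participants. Adjust for baseline score, HI severity, site or village where it can be estimated separately from arm, and baseline self-rated health. The equivalent is a mixed model of baseline and 24 months with baseline means constrained equal across arms and covariate effects allowed to differ by visit.

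- Replace ANOVA with this model.
- Handle missing 24-month scores by likelihood (mixed model) or multiple imputation (ANCOVA).
- Keep matching as a labelled sensitivity analysis outside intention to treat.
- Correct the Abstract so that structural equation modeling and cost-effectiveness carry the roles that the Statistical Analysis section gives them.
- Report HAU versus control with a plain statement that site and population are confounded with arm, whatever adjustment is shown.

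No new data are needed, since the scores, audiometry, site and self-rated health are already collected. The cost is wording plus the formal amendment and ethics approval that the Ethical Considerations section requires. Because follow-up is complete, the amendment should be dated before any outcome is examined by arm.

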### Data Collection and Management

Data collection forms and procedures for data management are available upon request. All the data will be collected through a structured paper questionnaire. Trained enumerators will conduct face-to-face interviews with each eligible participant and complete the forms. Double-blind data entry will be performed to input the baseline and follow-up data into electronic form for quality assurance purposes. All information collected during the trial will be kept in strict confidence. Participant details will be stored on a secure, password-protected computer disk and mobile hard disk drive. The confidentiality of the intervention objectives during qualitative interviews will be safeguarded by assigning a unique identification code to electronic sound files and transcripts of the interviews. The information will be known only to the qualitative researcher and appropriate members of the research team. The principal investigator (PI) and data analysis personnel will have access to the final trial dataset. According to the Good Clinical Practice guidelines, data will be archived for a period of 10 years after finalizing the study with participants’ informed consent. To enhance and protect participant confidentiality, any quotes published will be anonymous. After finalization, the key file containing information linking participants’ names and contact details will be destroyed once the project team no longer needs to contact the participants further for study purposes.

### Monitoring

#### Data Monitoring

The study is subject to local regulations. The principal investigator is responsible for developing, implementing, and maintaining the quality assurance and control of all the research. During the period of sample recruitment, an interim analysis will be conducted under strict confidentially, which may include analyses of data from other comparable trials. Through these interim analyses, the PI will determine if the interventions or potential mechanisms have been proven or if they differ from the expectations. The PI will decide whether to modify the trial. Unless this situation occurs, the research staff will remain unknown during the interim analysis.

#### Adverse Events

Adverse events will be collected and recorded after informed consent and this procedure will continue until the end of the study. For those who report an adverse event after submitting the signed informed consent but before the trial intervention, the event will not be considered as an adverse event related to our intervention. Serious adverse events will be reported to the ethics review committee.

#### Auditing and Inspecting

The PI will allow study-related audits and inspections by the ethics review committee of the documents pertaining to the research. The PI will guarantee the capability to conduct inspections of applicable study-related facilities.

### Ethical Considerations

The study was approved by the Chinese Ethics Committee of Registering Clinical Trials (ChiECRCT, Reference number: ChiECRCT20210561). The trial is registered on ClinicalTrials.gov (registration number: ChiCTR2200062148; date of registration: July 25, 2022). If there are any changes to the protocol, we will report to the ChiECRCT and inform the subjects. A formal amendment to the protocol will be submitted to and approved by the ethics review committee before implementation.

During the enrollment session, participants receive detailed information about the study and are required to provide written informed consent before undergoing the auditory examination. Regardless of their inclusion in subsequent studies, participants received compensation consisting of 30 Yuan (US $4.2) in cash and a gift of daily necessities for their participation in the hearing tests. In the follow-up survey, respondents will also receive 30 yuan (US $4.2) in cash after completing the questionnaire.

Each respondent is assigned a personal identification number, which serves as a unique identifier for correlating the participants’ identification details with information related to the trial, thereby safeguarding confidentiality. No further identifiable features will be included in the data analysis process.

## Results

### Trial Status

The project was funded in July 2019. The current protocol is version 3, dated January 15, 2025. The recruitment of participants and collection of baseline data began on September 1, 2022, and ended on September 30, 2022. A total of 435 participants were recruited and assigned to a random group at baseline. A follow-up survey was conducted after 24 months in September 2024, which included 397 participants. Figure 2 displays the flow diagram of the HISEA trial. Until this version of the protocol, the intervention effects have remained unknown.

**Figure 2 figure2:**
[figure not shown]
Hearing Impairment and Social Outcomes Evaluation in Adults study flow diagram developed using Standard Protocol Items for Interventional Trials or Consolidated Standards of Reporting Trials.

### Preliminary Results

Table 2 shows the sociodemographic characteristics of the sample at baseline. The mean (SD) age of the participants in RCT is 71.59 (SD 9.55) years, with 43.09% (187/434) of the sample identifying as female.

**Table 2 table2:** Baseline sample characteristics.

Variables		Control group	Hearing health education group	Hearing aid use group	Total
Age (years), mean (SD)		74.82 (9.29)	71.44 (6.51)	67.02 (11.75)	71.59 (9.55)
**Sex, n (%)**					
	Male	56 (35.9)	56 (35.67)	75 (61.98)	247 (56.91)
	Female	100 (64.1)	101 (64.33)	46 (38.02)	187 (43.09)
**Education, n (%)**					
	Illiterate	43 (27.74)	27 (17.2)	30 (25.21)	100 (23.2)
	Primary school	86 (55.48)	94 (59.87)	61 (51.26)	241 (55.92)
	Middle school or higher	26 (16.77)	36 (22.93)	28 (23.53)	90 (20.88)
**Marital status, n (%)**					
	With spouse	116 (75.32)	95 (67.14)	88 (76.52)	298 (72.86)
	No spouse	38 (24.68)	46 (32.86)	27 (23.48)	111 (27.14)
**Self-rated economic status, n (%)**					
	Fair	115 (74.68)	109 (70.32)	24 (20)	248 (57.81)
	Poor	39 (25.32)	46 (29.68)	96 (80)	181 (42.19)
**Self-rated health, n (%)**					
	Good	76 (48.72)	149 (94.9)	52 (42.98)	277 (63.82)
	Fair	65 (41.67)	7 (4.46)	46 (38.02)	118 (27.19)
	Poor	15 (9.62)	1 (0.64)	23 (19.01)	39 (8.99)
**Chronic disease, n (%)**					
	No	22 (20)	39 (27.08)	70 (61.4)	131 (35.6)
	Yes	88 (80)	105 (72.92)	44 (38.6)	237 (64.4)
Number of observations, n		156	158	121	435

## Discussion

### Principal Findings

We anticipate a significant positive effect of interventions on reducing social isolation and enhancing functioning outcomes, along with several psychological pathways, which contribute to these main results.

